#### Clinical impact measures

The impact of the interventions will be assessed on the proportion of patients that progress from early to late signs of deterioration and the quality of nursing care (primary measures). As per our previous studies we will use validated data extraction tools to mine data from patient observation charts. Appropriate frequency of vital signs and evidence-based responses to deterioration will be proxies for the quality of nursing care. Secondary measures include in-hospital mortality and admissions to ICU, and cost of provision of face-to-face versus web based education. We will also investigate stakeholder views and attitudes through semi-structured interviews with three key stakeholder groups at each site.

Patient sample size: Pilot data from an earlier rural study indicated that early signs of deterioration were present in 28 % of patients while late signs were present in 10 %, and that the total sample size required to detect a 5 % reduction in late signs of deterioration with a level of significance of 5 % and a power of 0.8 is 434 patients (217 before and 217 after the intervention) at each site [29].

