### Data collection tools

#### Patient medical records review

Using patients’ demography, diagnoses and vital signs data, outcomes will be measured in relation to deterioration including ICU admissions and mortality rates, etc. Further, based on our sample size calculations and the guidance produced by Harrison et al. [38], McQuillan [39] and NICE [40] we aim to identify a change in patient management by measuring the applicability of physiological observations, actions in relation to deterioration, and early and late signs of deterioration to identify improvements in performance (Table 2). We have developed and tested a chart audit tool based on a rationale for item inclusion, definitions, and clinical expert ratings of relevance and clarity with a high Content Validity Index of 0.83 [41]. We will therefore extract data from patient records from 80 randomly selected cases from each month, three months before the simulation intervention, and from each month for three months after the intervention (total *n* = 480 at each site). A post-hoc sensitivity analysis will be conducted to assess the representative nature of the sample.

**Table 2 Tab2:** Early and late signs of patient deterioration [Adapted from Harrison et al. [38]

Parameter	Early signs	Late signs
Oxygen saturation	90–95 %	<90 %
Systolic blood pressure (mmHg)	80–100 or 181–240	<80 or >240
Heart rate	40–49 or 121–140	<40 or >140
Respiratory rate	5–9 or 31–40	<5 or >40
Glasgow coma scale	N/A	>2 point drop

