#### Knowledge and skill performance ratings

Participant demographics, questionnaire, and simulation performance will be described with the use of descriptive and inferential statistics. Measures of dispersion (means, medians, etc.) will be reported. There will be a range of nominal, ordinal and interval data (paired and unpaired) requiring tests such as Chi-square; McNemar; Mann Whitney U; and t-tests. Multivariate analysis (linear and logistic regression) will be used to identify predictors of performance. Simulation exercises will be rated by two researchers for inter-rater reliability. A significance level of *p* < .05 will be applied throughout.

Based upon a Generic Qualitative Design eight stakeholder focus groups will be completed (two at each site) in order to identify the perceived impact of the program(s) [52]. Core themes and outcomes will be identified using Miles and Huberman’s stages of data analysis [53]. Analysts will attribute nominal codes to narrative segments and group narrative segments to identify key themes. Emergent themes will be shared and collaboratively refined to achieve a consensus for reporting. The reporting of findings will by guided by the COREQ guidelines for reporting qualitative research.

The program is designed to run for 18 months with a seven month lead-in, to enable literature reviews, ethical approval, access arrangements and refinement of data collection tools. The training intervention will be compressed into a four month period and subsequent patient notes review, data analyses and report writing will take a further seven months.

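### The 434 patients given as the before-plus-after total at each site is the number needed in each period, so per-site power is about 0.51 (0.55 with the charts planned), not 0.8

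*Protocol article*

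**What the plan says.** The sample size paragraph under Clinical impact measures takes its inputs from a rural pilot study, where "late signs were present in 10" % of patients. The aim is to "detect a 5 % reduction in late signs of deterioration" "with a level of significance of 5" %. The total for "a power of 0.8 is 434 patients (217 before and 217 after the intervention) at each site".

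Patient medical records review turns this into a sampling scheme, citing the sample size calculation as its basis: "We will therefore extract data from patient records from 80 randomly selected cases from each month, three months before the simulation intervention", and the same number "from each month for three months after the intervention (total *n* = 480 at each site"). That is 80 × 3 = 240 charts before and 240 after at each site.

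Late signs are a primary outcome (Aim and hypothesis; Clinical impact measures). The Data analysis section defines a successful intervention by statistical significance, including a reduction in the proportion with late signs.

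**The concern.** All the inputs for a two-proportion calculation are printed, and the result does not follow from them. Detecting 10 % against 5 % with 80 % power takes well over 400 patients per group, so 217 per period is about half of what is needed. The match between 434 and the per-group answer suggests that a per-group figure was read as a total and halved.

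The error carries into the data collection. The 240 charts per period look like a margin over 217, but they are 240 / 434.4 = 55 % of the number required. A reader who believes the power at each site is 0.8 would take a non-significant site result as fair evidence that the program did not work. If the full planned effect were present, the two-sided test at a single site would miss it about 45 % of the time.

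**Working it through.** **Inputs.** From Clinical impact measures: p1 = 0.10, a reduction of 5 points so p2 = 0.05, α = 0.05, power 0.80, and equal numbers before and after. From Patient medical records review: 240 per period per site. Assumed, because the article does not say: a two-sided test, independent patients in the two periods, and a simple before-after comparison.

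**Required number per period**

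n = [z(α/2)·√(2·p̄·(1−p̄)) + z(power)·√(p1(1−p1) + p2(1−p2))]² / (p1−p2)², with p̄ = 0.075

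- First term: 1.96 × √(2 × 0.075 × 0.925) = 1.96 × 0.3725 = 0.7301
- Second term: 0.8416 × √(0.0900 + 0.0475) = 0.8416 × 0.3708 = 0.3121
- n = (0.7301 + 0.3121)² / 0.0025 = **434.4 per period**, rounded up to 435, or 870 per site

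This reproduces the printed 434 as a per-period number. It does not reproduce 434 as a total, or 217 per period.

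**Power at the stated and planned numbers**

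Power = Φ[(0.05·√n − 0.7301) / 0.3708]. For the one-sided test, 0.7301 becomes 1.645 × 0.3725 = 0.6127.

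| Patients per period | Two-sided | One-sided |
|---|---|---|
| 217 (stated, one site) | 0.507 | 0.631 |
| 240 (planned, one site) | 0.548 | 0.669 |
| 434 | 0.800 | 0.876 |
| 480 (planned, two sites pooled) | 0.838 | 0.904 |
| 960 (planned, four sites pooled) | 0.986 | – |

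Exact enumeration of the uncorrected chi-square test gives two-sided power of 0.508 at 217 and 0.553 at 240. With 240 per period, 80 % two-sided power exists only for a fall from 10 % to about 3.6 %.

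**Other readings of the calculation**

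- Other two-sided formulas, per period: 432 with unpooled variance, 436 with pooled variance throughout, 424 with the arcsine transformation, 474 with continuity correction.
- One-sided 5 %: 342.1, so 343 per period.
- A relative 5 % reduction (10 % to 9.5 %): about 55,000 per period.
- Progression among patients with early signs. Assume every late-sign patient is among the 28 % with early signs, and that the rate among them falls from 10/28 to 5/28. This needs 96 early-sign patients per period, or 96 / 0.28 = 343 patients. One-sided it needs 75, or 75 / 0.28 = 268. Both exceed 240.

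None of these gives 217 per period. Numbers near 217 appear only if the stated design or inputs change, for example 223 for a one-sided test of 10 % against 4 %.

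**The case against.** The arithmetic is hard to dispute. The case on the other side concerns what follows from it.

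1. **Sidedness is not stated, and the hypotheses are directional.** The article says only that "A significance level of *p* < .05 will be applied throughout". This is fair as far as it goes: one-sided power would be 0.63 to 0.67, and the miss rate at a site with the planned charts about one in three. But 434 is reproduced by the two-sided formula and not by the one-sided one, and neither reaches 0.8 at a site.
2. **The halving is inferred.** The article shows no derivation and points to a cited study. This stands, although the match is very close. The power shortfall does not depend on how the error arose.
3. **No section defines a confirmatory test at site level.** The hypotheses concern the two education models, and the design compares groups of two wards each. This also stands. If the late-sign test is done by program, the planned 480 against 480 gives about 0.84, and the fault is a wrong justification more than a demonstrated lack of power. But the claim of 0.8 power is attached to each site in the article's own words, and the chart sample is set per site.
4. **The pooled power is optimistic.** It assumes no ward-by-period variation, with only two wards per program. With illustrative design effects of 1.1, 1.2 and 1.5 (assumed values, effective n of 436, 400 and 320), 0.84 falls to about 0.80, 0.77 and 0.67. So the planned charts suffice at program level only under that condition.
5. **A time series analysis is planned.** The calculation is worded as a before-after comparison of a proportion. Nothing in the article ties 217 + 217 to a time series model, and three monthly points per period give no reason to expect more power.

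**Conclusion.** The concern holds. The stated inputs require about 435 patients in each period at each site, not 434 in total. Power at a site is about 0.51 with the stated 217 per period and about 0.55 with the planned 240, against the 0.8 claimed. These figures assume a two-sided test, an absolute fall from 10 % to 5 %, and independent patients. A one-sided test would raise them to 0.63 and 0.67. Because this is the only power statement for a primary outcome and it sets the size of the chart review, it must be corrected. The trial as a whole is not necessarily underpowered: testing by program gives about 0.84 before any allowance for ward-by-period variation.

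**What to change.** Replace the sample size statement with one to this effect: for a fall in late signs from 10 % to 5 %, two-sided 5 % significance and power 0.8, about 435 patients are needed in each period (870 in total); the 240 per period planned at one site give power of about 0.55.

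Add one sentence naming the level of the late-sign test. The program level fits the first hypothesis: pool the two sites of each program, 480 before against 480 after, with site as a fixed factor and power of about 0.84. State that this power assumes no extra ward-by-period variation and would be lower with it. Label site-level results descriptive. On that condition no further charts are needed.

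If 80 % power at each site is really wanted, the sample must grow to 435 / 3 = 145 charts per month. That is 870 − 480 = 390 more per site, or 1,560 more over four sites.

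The first route costs one corrected paragraph, one added sentence and a less favourable per-site figure. Since Study status says data collection has begun, the correction should be dated and made before the late-sign outcome is analysed.

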### Aim and hypothesis

This research aims to measure the impact of two forms of simulation education on nurses’ ability to detect and manage patient deterioration, to assess patient outcomes and to compare the total costs between the two interventions. The research hypotheses to be tested are:(i).Both the face-to-face and web-based models of simulation education will improve the detection and management of patient deterioration and patient outcomes.(ii).The web-based program will have lower total costs in improving the detection and management of patient deterioration and patient outcomes.

The primary outcomes to be measured are the proportion of patients showing late clinical signs of deterioration, and the quality of nursing assessment. The secondary outcomes to be measured are the cost of provision of face-to-face versus web-based training, together with stakeholders’ views and attitudes regarding the forms of program delivery, and change to in-hospital mortality and the rate of admission to ICU (see Fig. 1).

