### Data analysis

Patient notes review: a pre-post intervention analysis through time series analyses. The appropriateness of observations, incidence of late signs of deterioration, in-hospital mortality and admissions to ICU will be used as the primary measures of patient management. Successful intervention will be identified by a statistically significant increase in applicable actions and a reduction in the proportion of late signs, in-hospital mortality and admissions to ICU.

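### Sample size and 80% power are stated per site, but the hypothesis is per program and the success rule names no unit; the power is reached only with a program's two sites combined

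*Protocol article*

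**What the plan says.** Three places in the protocol article bear on the unit of the pre-post decision, and they do not agree.

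- **Sample size (Clinical impact measures).** The baseline is that "late signs were present in 10" per cent of patients. The aim is to "detect a 5 % reduction in late signs of deterioration" "with a level of significance of 5 % and a power of 0.8", and the number required is "434 patients (217 before and 217 after the intervention) at each site". Patient medical records review then plans 80 charts a month for three months before and "from each month for three months after the intervention (total *n* = 480 at each site"). Size and power are both attached to the site.
- **Hypothesis and design.** Aim and hypothesis says: "Both the face-to-face and web-based models of simulation education will improve the detection and management of patient deterioration and patient outcomes". Methods/design describes comparisons within and between Group 1 (web-based) and Group 2 (face-to-face). The Participants section gives each group two wards. The unit here is the program.
- **Success rule (Data analysis).** "Successful intervention will be identified by a statistically significant increase in applicable actions and a reduction in the proportion of late signs"; the same sentence goes on to require falls in in-hospital mortality and ICU admissions. It does not say whether this is read in a site, in a program or over all four wards.

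**The concern.** The unit that carries the power is not the unit that carries the hypothesis, and the rule that turns results into a conclusion is tied to neither. If the analysis follows the sample-size sentence, it yields four site results per outcome. Nothing stated then says how two site results become one conclusion about a program, or what follows when one site is significant and the other is not.

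This matters more if the site is too small to deliver the power claimed for it, because disagreement between sites then becomes the ordinary outcome of an effective program. So the question to check is at which level the stated 80% power actually holds.

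**Working it through.** **Inputs from the protocol.** Late signs 10% before. A reduction of 5%, read as absolute (10% to 5%), because a relative reading (10% to 9.5%) would need about 55,000 charts per period. Significance 5%, power 0.8. 217 + 217 charts per site required. 80 × 3 = 240 charts per period per site planned. Two sites per program.

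**Assumptions.** Two-sided test (sidedness is not stated; one-sided results are also given), independent charts, no time trend, same effect at every site.

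**Step 1: the plan's own figure.** With p1 = 0.10, p2 = 0.05 and mean 0.075, the two-proportion formula per period is

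n = [1.96 × √(2 × 0.075 × 0.925) + 0.842 × √(0.10 × 0.90 + 0.05 × 0.95)]² / 0.05²

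= [1.96 × 0.3725 + 0.842 × 0.3708]² / 0.0025 = 434.4.

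So 434 matches the number needed in **each period**, not the total over both. Variants do not rescue 217 per period: unpooled variance gives 432, arcsine 424, and one-sided 5% gives 343.

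**Step 2: power by unit.** Power = Φ{[0.05 × √n − 1.96 × 0.3725] / 0.3708}.

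| Unit | Charts per period | Power, two-sided 5% | Power, one-sided 5% |
|---|---|---|---|
| One site, as required | 217 | 0.51 | 0.63 |
| One site, as planned | 240 | 0.55 | 0.67 |
| One program (2 sites), as required | 434 | 0.80 | 0.88 |
| One program (2 sites), as planned | 480 | 0.84 | 0.90 |
| All four wards, as planned | 960 | 0.99 | 0.99 |

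The stated 0.8 is missed at a site under either sidedness. It is met once a program's two sites are combined, since 2 × 217 = 434 per period.

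**Step 3: disagreement between a program's two sites** when the planned effect is present at both: 2 × power × (1 − power).

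- 217 per period: 2 × 0.507 × 0.493 = 0.50.
- 240 per period: 2 × 0.548 × 0.452 = 0.50. Both sites are significant in 0.548² = 0.30 of trials and neither in 0.452² = 0.20.

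**Step 4: consequence of fixing the program as the unit** (480 per period).

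- Both programs significant on late signs: 0.838² = 0.70.
- If a second primary outcome must also succeed, with equal power and independence (both assumed): 0.838⁴ = 0.49.

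**The case against.** The best reply is that the unit can be worked out. The design statement and hypothesis (i) both point to the program, an intervention in the success rule most naturally means a program, and the per-site numbers can be taken as chart quotas rather than as four separate tests. How sites are combined and how discordant sites are handled is also normal material for an analysis plan, which is not shown here. Much of this stands: the program is the natural unit, and a missing label alone would be a small matter. It does not dispose of the point, because the sample-size sentence states a required number at each site for a given power, and that statement is wrong at that level wherever the analysis plan places the test.

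A reader might go further and infer a multiplicity failure: site, program and pooled tests of both primaries, each at 5%, with any one of them enough for success. The protocol does not support this. It nowhere says that all these tests will be run. Its success rule joins the outcomes with 'and', and hypothesis (i) says both programs. The sentence "A significance level of *p* < .05 will be applied throughout" stands under the knowledge and skill ratings, so its reach to the chart review is uncertain. If both primaries must be significant in the beneficial direction in the same unit, the chance of a false success in any of the seven possible units (four sites, two programs, one pooled) is about 0.004 at correlation 0 and 0.06 at correlation 0.8. If only the rise in applicable actions must be significant and late signs need merely fall, it is about 0.09 over four sites at correlation 0.5, before the mortality and ICU conditions lower it further.

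Nor do the units give contradictory findings in the sense of benefit against harm. They differ only in whether a result is significant.

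**Conclusion.** The point holds as a mismatch of units with a wrong stated power. The protocol claims 80% power per site; its own inputs give about 0.51 to 0.55 there and about 0.84 for a program. With a true fall from 10% to 5% everywhere, a program's two sites would split on significance in about half of trials, with no stated rule for reading the split.

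The figures rest on a simple two-proportion test with independent charts and an equal effect at each site. Clustering within wards and months, or adjustment for a time trend in the planned time series analysis, would generally lower all of these powers, so 0.84 is an optimistic value for the program too. The size of any such loss cannot be derived from the protocol. No claim of an inflated family-wise error is made.

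**What to change.** In Clinical impact measures and Data analysis, before the chart outcomes are analysed:

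1. Name the deciding contrast as the pre-post change for each program, combined over its two sites and stratified by site within the planned time series analysis.
2. State that hypothesis (i) is supported only if both programs meet the success rule.
3. Report single-site and four-ward results as descriptive, with confidence intervals and no success verdict.
4. Restate the sample size as 480 charts per period per program, with power of about 0.84 for late signs falling from 10% to 5% (two-sided 5%, simple two-proportion test, before any allowance for clustering or time trend).

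The cost is wording and a site-stratified model; no chart is added. The downsides should be stated openly. Sites lose their own verdict. If a program's two sites respond differently, the combined estimate is an average, which the site intervals will show. The chance that both programs succeed is at most about 0.70 for late signs alone, and lower once the other required outcomes are added: about 0.49 with one further primary of equal power and independent of the first.

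### The stated power of 0.8 assumes independent charts and makes no allowance for month-to-month variation within a ward, on top of a per-period number used as the total

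*Protocol article*

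**What the plan says.** The patient sample size paragraph under Clinical impact measures takes pilot data in which "late signs were present in 10" per cent of patients, and sets the aim to "detect a 5 % reduction in late signs of deterioration" "with a level of significance of 5 % and a power of 0.8". The result is "434 patients (217 before and 217 after the intervention) at each site". No correlation, design effect or between-month variance appears.

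Patient medical records review fixes the sampling: "80 randomly selected cases from each month, three months before the simulation intervention", and the same for three months after, giving "total *n* = 480 at each site". Participants describes one medical ward at each of four hospitals, two wards per program. The pre-post contrast is therefore three ward-months against three at a site, and six against six in a program.

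Data analysis plans a pre-post comparison of the notes by time series methods, names no model, and defines success by statistical significance. The 5% level that "will be applied throughout" is stated under Knowledge and skill performance ratings.

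**The concern.** A formula for independent proportions counts only binomial sampling error. Charts from the same ward and month plausibly share staffing, workload and season. Comparing a ward with itself removes stable differences between wards, but not its variation from month to month. If such variation exists, 80 charts in one month carry less information than 80 independent charts, and true power lies below the calculated value.

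The reader at risk is one who notices that 240 per period is too few at a site, pools the two wards of a program to reach 480, and takes the resulting 0.84 as secure. Correcting the total-versus-per-period error alone does not guarantee 0.8.

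**Working it through.** **Inputs.** From Clinical impact measures: p1 = 0.10; p2 = 0.05 (reading the 5% reduction as absolute); alpha 0.05 (taken as two-sided, since sidedness is not stated); power 0.8. From Patient medical records review: 80 charts per month, so 3 × 80 = 240 per period per site and 2 × 240 = 480 per period per program. The correlation rho between charts of the same ward-month is **assumed**.

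**1. The plan's own figure.** With pbar = 0.075,

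n per period = [1.96 √(2 × 0.075 × 0.925) + 0.8416 √(0.10 × 0.90 + 0.05 × 0.95)]² / 0.05² = 434.4.

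So 434 is the number per period. Other variants give 432 (unpooled), 424 (arcsine), 474 (continuity-corrected), 343 (one-sided) and 382 (one-sided, continuity-corrected). None gives 217 per period. A relative 5% reduction (10% to 9.5%) would need 55,252 per period.

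**2. Power with independent charts.** Power = Φ{[0.05 √n − 1.96 √(2 × 0.075 × 0.925)] / √0.1375}: 0.51 at n = 217, 0.55 at 240, 0.80 at 434, 0.84 at 480. One-sided, it is 0.63 at 217 and 0.67 at 240.

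**3. Allowance for ward-months.** Design effect DE = 1 + (80 − 1) rho; replace n by n/DE in step 2. The error rate of a test that ignores rho is 2[1 − Φ(1.96/√DE)].

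| Assumed rho | DE | Power per site (240 per period) | Power per program (480 per period) | Error rate if charts are tested as independent |
|---|---|---|---|---|
| 0 | 1 | 0.55 | 0.84 | 5% |
| 0.001 | 1.08 | 0.52 | 0.81 | 6% |
| 0.005 | 1.40 | 0.42 | 0.70 | 10% |
| 0.01 | 1.79 | 0.34 | 0.59 | 14% |
| 0.02 | 2.58 | 0.25 | 0.45 | 22% |

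For scale, at a 10% rate rho = 0.005 is a month-to-month standard deviation of √(0.005 × 0.10 × 0.90) = 0.021, about 2 percentage points. The step from 217 to 240 charts (240/217 = 1.106) would cover only rho = 0.106/79 = 0.0013, and the document does not present it as an allowance for clustering.

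**4. Power of a test that estimates the between-month variance.** The powers in step 3 are large-sample approximations and do not apply to a t-test on ward-month proportions. For that test the residual degrees of freedom are 6 − 2 = 4 at a site, and 12 − 2 (wards) − 1 (period) = 9 in a program, or 8 with a ward-by-period term. The non-centrality is 0.05/√(0.1375 × DE/n). At rho 0 / 0.005 / 0.01 / 0.02, power is about 0.36 / 0.28 / 0.23 / 0.17 per site and 0.75 / 0.61 / 0.51 / 0.38 per program. Simulated at the month level, this test keeps its error rate at about 5%.

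**The case against.** Three objections have force.

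- **Clustering is not the main reason that 0.8 fails.** A reader might infer from the ward-month sampling that correlation explains the shortfall. It does not: power at a site is 0.51 to 0.55 at zero correlation, because the per-period number was used as the total. Clustering only adds to that loss.
- **The size of the added loss is assumed.** The document gives no month-level correlation, and stable ward differences cancel. At 0.001 the effect is slight: 0.52 against 0.55 per site, and 0.81 per program, still above 0.8.
- **A failure of the 5% threshold is not established.** A reader might also infer that the false-positive rate is inflated as planned. That requires charts to be tested as independent, and nothing in the document says so. Data analysis plans time series methods, which can carry month-to-month variation, and the model may be in an analysis plan not shown. The sentence fixing the 5% level sits with the nurse knowledge and skill ratings.

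All three stand as limits on the point. None removes it: the power statement is in this document, and its formula has no between-month term. A time series analysis that respects months protects the error rate but does not restore the power, since it works from six monthly values per site.

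**Conclusion.** The point holds in a limited form. The 0.8 rests on independent charts and ignores month-to-month variation within a ward, although sampling is by ward-month. This is secondary to the halved sample size, which by itself leaves power at 0.51 (217 per period) or 0.55 (240 per period) at a site.

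Under assumed correlations of 0.001 to 0.02, approximate power falls to between 0.52 and 0.25 per site and between 0.81 and 0.45 per program. The inflated error rate of about 6% to 22% over the same range is conditional on a patient-level test that the document does not specify. The figures assume a two-sided 5% level, an absolute fall from 10% to 5%, and exactly 80 charts in every month.

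**What to change.** 1. In the patient sample size paragraph, correct 434 to a per-period number and state that 0.8 assumes independent charts. Restate power per site and per program over the range of correlations above, labelled as assumed.
2. Under Data analysis, state that the time series pre-post comparison must carry between-month variance within ward. One suitable form is a model on ward-month proportions with ward and period effects and the residual between-month variance, referred to a t distribution with 9 residual degrees of freedom per program (8 with a ward-by-period term).
3. If that test is used, quote its own power from step 4 of the working, not the large-sample values.

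The cost is text only; no extra charts are needed. The downside is a lower stated power and wider intervals. Some power is lost even if months do not vary at all: per program, about 0.75 in place of 0.84.
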